### Data analysis and management

3.9

#### Data collation

3.9.1

Data will be collected using CRFs, capturing baseline characteristics, intervention records, laboratory results, and scale scores. All biological specimens will be de-identified via unique codes to protect participant privacy. Statistical analyses will be performed using SPSS 22.0, with the following approach:

① Statistical Tests by Data Type: Categorical variables will be summarized as frequencies (percentages) and compared using the chi-square test. Continuous variables will be presented as mean ± standard deviation; after testing for normality and homogeneity of variance, parametric data will be analyzed using *t*-tests (independent or paired, as appropriate), while non-parametric data will be analyzed using the Mann–Whitney *U* test (rank-sum test). Ordinal data (e.g., scale scores) will also be analyzed using non-parametric rank-sum tests.

② Analysis of Primary and Secondary Outcomes: Outcomes include scale scores (GIDS, HAMA, HAMD, SF-36, and PSQI), brain function parameters (EEG, fNIRS-derived rCBF), gut microbiota metrics (diversity indices, taxon abundance), and biochemical markers (IL-6, TNF-α, 5-HT, and BDNF). A stratified multiple comparison adjustment will be applied: the primary outcome will use Bonferroni correction (corrected α = 0.01, accounting for five indicators), while secondary outcomes and biomarkers will use the False Discovery Rate (FDR) method (FDR = 0.05). Subgroup analyses (e.g., by gender, Stanford type) will also employ FDR correction to control Type I error inflation.

③ Correlation Analysis: Multiple linear regression will be used to explore associations between clinical outcomes, gut microbiota, inflammatory markers, and brain function.

④ Significance Level: A two-sided *P* value < 0.05 will be considered statistically significant for all tests, unless otherwise specified after multiplicity adjustment.

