**Methods:**

This is a single-center, randomized, investigator-blinded, sham-controlled randomized controlled trial. A total of 50 patients aged 18–75 years with postoperative Stanford Type A or B AD will be enrolled and randomly assigned in a 1:1 ratio to either the active taVNS group or the sham control group. Both groups will receive standard postoperative care. The experimental group will additionally receive active taVNS targeting the vagus nerve-innervated auricular area (15 Hz, 200 μs pulse width), while the control group will receive sham stimulation at a non-vagus innervated site without electrical current. The intervention will be administered for 30 min, twice daily, over 7 consecutive days, with follow-up assessments continuing until 24 weeks post-surgery. Primary outcomes include changes in gut microbiota diversity/abundance and brain function (assessed via functional near-infrared spectroscopy). Secondary outcomes encompass inflammatory markers, plasma neurotransmitter levels, intestinal function recovery, and relevant psychometric scale scores. Safety will be monitored through vital signs, laboratory tests, and recording of any adverse events.

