#### Main outcome measures

3.6.1

① Gut Microbiota Diversity and Abundance: Fecal samples will be analyzed using metagenomic sequencing. Key metrics will include the abundance of probiotics (e.g., Bifidobacterium, Lactobacillus)—where reduced abundance reflects gut microbiota imbalance and indicates dysbiosis—the abundance of opportunistic pathogens (e.g., Escherichia coli, Enterococcus)—whose excessive proliferation may disrupt the intestinal barrier and induce systemic inflammation—and diversity indices (the Shannon index, which integrates species richness and evenness, with higher values indicating greater diversity; and the Simpson index, which emphasizes the dominance of key species, with lower values indicating greater diversity). These metrics will be used to evaluate the severity of postoperative gut microbiota dysbiosis in AD patients and the regulatory effects of taVNS on the microbiota.

② Brain Function Changes:

a. BCI-Related Metrics: Electroencephalography (EEG) will be used to record brain electrical activity. Measures will include EEG rhythms (α-waves: 8–12 Hz, reflecting a state of cerebral relaxation and correlating with cognitive function; β-waves: 12–30 Hz, associated with motor preparation/execution and serving as an indicator of neuroplasticity), Event-Related Potentials (ERPs: where P300 latency reflects cognitive processing speed, and P300 amplitude reflects attention engagement), Motor-Related Potentials (MRPs: which evaluate neural signals related to motor intention), and motor imagery ability (detected via BCI, reflecting the potential for motor function recovery). Together, these measures enable real-time monitoring of taVNS-induced activation of the cerebral motor cortex.b. fNIRS-Related Metrics: This non-invasive method will measure regional cerebral blood flow (rCBF). Assessments will include cerebral metabolic activity (inferred from changes in oxyhemoglobin and deoxyhemoglobin concentrations in the prefrontal cortex and motor cortex, where reduced concentrations may indicate impaired brain function) and brain region activation patterns (evaluated through the hemodynamic responses of specific brain regions during cognitive tasks to assess prefrontal executive function and motor cortex coordination, with abnormal patterns suggesting neurological dysfunction). This approach allows for non-invasive monitoring of taVNS-mediated improvements in postoperative brain function.

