Although recent studies on taVNS have confirmed its anti-inflammatory, intestinal regulatory, and neurotransmitter-balancing effects in common postoperative conditions such as insomnia (27), anxiety and depression (28), constipation (29), cognitive impairment (30), and postoperative subarachnoid hemorrhage (31), its application in AD postoperative complications has not been reported. This study employs primary outcome measures—including gut microbiota diversity and abundance, BCI-related indicators, and fNIRS-related indicators—as well as secondary measures such as inflammatory factors, neurotransmitters, intestinal function, and relevant scale scores to determine the efficacy and mechanism of taVNS in regulating the GBA for treating AD postoperative complications. In a mouse model of constipation-predominant irritable bowel syndrome, taVNS has been shown to restore *Lactobacillus* abundance, increase probiotics like *Bifidobacterium*, and improve defecation function, gastrointestinal transit, and visceral hypersensitivity; the regulation of gut microbiota is an important mechanism underlying these effects (13). Combined with EEG analysis of BCI-related indicators, studies have found that taVNS can improve learning performance, reduce the amplitude of movement-related cortical potentials and the α–γ modulation index, and enhance frontal lobe functional connectivity. Furthermore, EEG reveals that taVNS improves motor learning by enhancing cognitive memory (32). fNIRS can detect that taVNS improves accuracy in the No-Go task (which requires inhibition of responses to specific stimuli), reduces information accumulation in the Go task (which requires responses to target stimuli), enhances engagement of the bilateral inferior frontal gyrus and prefrontal network connectivity, and improves emotional inhibition. Thus, fNIRS helps elucidate the neural mechanisms of taVNS (33). Previous studies have shown (34) that taVNS can ameliorate depression-like behaviors in a lipopolysaccharide (LPS)-induced rat model of inflammatory depression, regulate peripheral pro-inflammatory factors (e.g., IL-1β, TNF-α) and anti-inflammatory factors (e.g., IL-4, IL-10), and inhibit activation of the NF-κB pathway in the prefrontal cortex, thereby playing a key role in modulating the peripheral-central inflammatory network. taVNS is thought to exert its effects through the vagus nerve's “cholinergic anti-inflammatory pathway.” Specifically, its anti-inflammatory effect at 15 Hz is superior to that at 25 Hz: it can reduce levels of inflammatory factors, immune cell infiltration, and tissue damage, showing feasibility for treating acute inflammation (35). Additionally, taVNS's regulation of central neurotransmitters (5-HT and BDNF) may alleviate postoperative anxiety and depression and improve cognitive function, thereby interrupting the vicious cycle of psychological stress and abnormal vascular tone (36, 37). Scores from multidimensional scales, including the GIDS, HAMA, HAMD, SF-36, and PSQI, can also reflect the improvement of various clinical symptoms and the interventional efficacy in postoperative AD patients.

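### The Bonferroni threshold of 0.01 is set for five primary indicators that are never identified and that do not match the primary variables listed, so a 5% family-wise error is not assured

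*Protocol article*

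**What the plan says.** Section 3.9.1 sets the rule for primary outcomes: "the primary outcome will use Bonferroni correction (corrected α = 0.01, accounting for five indicators". Secondary outcomes and biomarkers go to an FDR procedure at 0.05. The default elsewhere is a two-sided P below 0.05, which "will be considered statistically significant for all tests, unless otherwise specified after multiplicity adjustment".

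The primary outcomes are described in four places:

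- **Section 3.6.1, microbiota:** "Key metrics will include the abundance of probiotics (e.g., Bifidobacterium, Lactobacillus"), "the abundance of opportunistic pathogens (e.g., Escherichia coli, Enterococcus"), and "diversity indices (the Shannon index, which integrates species richness and evenness, with higher values indicating greater diversity; and the Simpson index".
- **Section 3.6.1, brain function:** a BCI block that opens "Measures will include EEG rhythms" and goes on to P300 latency and amplitude, motor-related potentials and motor imagery. A separate fNIRS block covers oxy- and deoxyhemoglobin in two cortical regions, plus activation patterns.
- **Section 3.9.2:** four variables from the primary domains are named for the linear mixed model: Shannon index, Bifidobacterium abundance, fNIRS rCBF and EEG α-wave power. The list is introduced as an inclusion, not as complete.
- **Abstract and Discussion:** the abstract has "Primary outcomes include changes in gut microbiota diversity/abundance and brain function (assessed via functional near-infrared spectroscopy"), with no EEG. The Discussion has "primary outcome measures—including gut microbiota diversity and abundance, BCI-related indicators, and fNIRS-related indicators".

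**The concern.** A Bonferroni divisor protects the family-wise error only if it is at least the number of tests that can produce a primary claim. Here the divisor is fixed at five, while the text that defines the primary outcomes lists many more variables and marks none of them as the five. Two things are at stake. If every listed variable is tested at 0.01, the overall false-positive rate exceeds the intended 5%. If only five are tested, nothing on the page says which, so the choice could be made after the results are seen. Either way, a primary success could not be read as a result at the 5% level.

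**Working it through.** **1. The plan's own figure.** 0.05 / 5 = 0.01, so the stated threshold is reproduced. Five independent tests at 0.01 give 1 − 0.99^5 = 0.049, and the Bonferroni bound is 5 × 0.01 = 0.05. The arithmetic is correct for five tests.

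**2. Counting Section 3.6.1.**

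| Block | Variables | Count |
|---|---|---|
| Microbiota | Bifidobacterium, Lactobacillus, E. coli, Enterococcus, Shannon, Simpson | 6 |
| EEG/BCI | α, β, P300 latency, P300 amplitude, motor-related potentials, motor imagery | 6 |
| fNIRS | oxy- and deoxyhemoglobin (2 if regions are pooled, 4 if separate) plus activation (1, or 2 if per region) | 3 to 6 |
| Total | | 15 to 18 |

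Separate regions with one activation measure give 6 + 6 + 5 = 17. The four taxa are examples, so the list could grow.

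**3. Looking for five elsewhere.**

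- Abstract: two domains, with brain function by fNIRS only.
- Section 3.9.1: four primary groupings (EEG, fNIRS, diversity indices, taxon abundance).
- Section 3.9.2: four named variables.
- Section 3.6.1 by heading: probiotics, opportunistic pathogens, diversity indices, BCI, fNIRS. This does make five, but they hold 2, 2, 2, 6 and 3 to 6 variables respectively, and no composite or lead variable is defined for any of them.

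**4. Family-wise error if each listed variable is tested once at 0.01, with no true effect on any.** Under independence, FWER = 1 − 0.99^m:

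- m = 15: 0.140
- m = 17: 0.157
- m = 18: 0.166

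For equally correlated two-sided z-tests with common correlation ρ and c = z(0.995), FWER = 1 − E[{Φ((c − √ρ·X)/√(1−ρ)) − Φ((−c − √ρ·X)/√(1−ρ))}^m], with X standard normal. By numerical integration with m = 17:

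| ρ (assumed) | 0.3 | 0.5 | 0.7 | 0.8 | 0.9 |
|---|---|---|---|---|---|
| FWER | 0.135 | 0.106 | 0.074 | 0.056 | 0.037 |

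The document gives no correlations, so the whole range is an assumption.

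**5. The narrow readings.** Four tests at 0.01 give 1 − 0.99^4 = 0.039. Two tests would allow 0.05/2 = 0.025 each. On these readings 0.01 is conservative.

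**6. Would a stricter divisor be practical?** For 17 tests the threshold would be 0.05/17 = 0.0029. With Section 3.3's inputs (difference 3, SD 5) and 25 per group, the standardised difference is 3 / (5 × √(2/25)) = 2.12. Power is Φ(2.12 − z): 32% at 0.01 (z = 2.576) and 20% at 0.0029. Shortening the list is therefore more workable than dividing further. The gap between these powers and the 80% claimed in Section 3.3 is a separate matter.

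**The case against.** The best defence is that five can be found. Section 3.6.1, read by its headings, yields three microbiota groups and two brain-function groups, and with one test per group 0.01 is exactly right. That stands as a possible reading. It means a reader should not infer that the divisor is wrong on every interpretation, particularly as the narrower lists in Section 3.9.2 and the abstract make 0.01 conservative. Nor should a reader infer that the number was taken from the five secondary scales named in the same paragraph, because the sentence ties it to the primary outcome.

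A second tempting step is to multiply by the three post-baseline visits. Seventeen variables at three visits would be 51 tests and, if independent, 1 − 0.99^51 = 40%. The document does not support that figure. It never says visits are tested separately, and the mixed model in Section 3.9.2 allows one test per variable. The choice of contrast may properly sit in an analysis plan that is not shown.

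It is also fair that 15 to 18 is a count made here, that the taxa are examples, and that related measures such as Shannon and Simpson will be correlated, so the independence figures are towards the high end.

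This does not remove the point. Each of the five headings contains several variables without a defined single test, so the reading that rescues 0.01 is not written down. Nor is this just detail left for later: the article itself fixes the threshold and the number, and the number does not fit the family it lists.

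**Conclusion.** The point holds as a mismatch between a stated threshold and the stated primary family. The five indicators are not identified, and testing the variables in Section 3.6.1 at 0.01 does not guarantee a 5% family-wise error. Under independence the error is about 14% to 17% for 15 to 18 tests. For 17 tests it is 13.5% at correlation 0.3 and 10.6% at 0.5. It falls below 5% only at very high common correlation (3.7% at 0.9), which the document gives no reason to expect across stool taxa, EEG and fNIRS.

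These figures assume one test per listed variable, each able to support a primary claim. They do not apply if exactly five tests, or fewer, are run. The defect in that case is that the choice is open, not that the error is inflated. Testing visits separately would raise the error further, but the document does not state that this will be done.

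**What to change.** Before any unblinded look, do one of the following:

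- Name exactly five primary variables, each with one contrast or visit, and keep 0.01.
- Name fewer, and set the threshold at 0.05 divided by their number, or use Holm.

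Move every other microbiota, EEG and fNIRS variable to the FDR tier that Section 3.9.1 already provides. State whether EEG/BCI is primary, and make the abstract and Sections 3.6.1, 3.9.1 and 3.9.2 list the same variables. If a heading such as probiotic abundance is meant to be one indicator, define the single quantity tested.

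The cost is a change of wording, with no new data collection. The downside is small: most of the listed variables lose primary status, although they are still measured and reported.

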### Sample size estimation

3.3

The sample size for this study was calculated using the standard formula for comparing means between two independent groups in a randomized controlled trial. The formula and parameters are defined as follows: Sample Size Calculation Formula:

$$\begin{array}{c} n=2\times {\left[\frac{\left(Z_{\alpha /2}+Z_{\beta /2}\times \sigma \right)}{\Delta }\right]}^{2} \end{array}$$
(1)

Where: *n* = sample size per group; *Z*_α_/2 = critical value for a two-tailed test at significance level α; *Z*_β_ = critical value for Type II error rate β; σ= population standard deviation of the primary outcome; Δ = minimum clinically important difference.

Basis for Parameter Setting: *Z*_α_/2: A two-tailed significance level (α) of 0.05 was used, corresponding to *Z*_α_/2 = 1.96; *Z*_β_: A statistical power (1 – β) of 80% was targeted (β = 0.2), corresponding to *Z*_β_ = 0.84; Δ and σ: Based on previous taVNS randomized controlled trials (17–19) and our pilot data, we assumed a continuous primary outcome (e.g., postoperative quality of life score or change in serum IL-6). The expected between-group difference (Δ) was three points, with a common standard deviation (σ) of five points.

Sample Size Calculation Result: Using the above parameters, 22 participants were required per group, yielding an initial total sample size of 44. Accounting for an anticipated 10% dropout rate, the final sample size was increased to 50 participants. These will be randomly assigned at a 1:1 ratio to the intervention (taVNS, *n* = 25) and control (sham stimulation, *n* = 25) groups.

Power analysis was performed for the primary outcomes (gut microbiota and brain function). The final sample size ensures ≥80% power for both. This sample size also covers the secondary endpoints and no separate calculation was needed.

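### Holm's step-down test could replace single-step Bonferroni for the five primary indicators: same 5% family-wise error, never fewer rejections, and a small gain in power if several indicators respond

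*Protocol article*

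**What the plan says.** In the protocol article, section 3.9.1 (Data collation), item ②, "the primary outcome will use Bonferroni correction (corrected α = 0.01, accounting for five indicators". Secondary outcomes, biomarkers and subgroup analyses get a false discovery rate method instead. Item ④ of the same section says that a two-sided P value below 0.05 "will be considered statistically significant for all tests, unless otherwise specified after multiplicity adjustment".

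Section 3.3 (Sample size estimation) supplies the design values:

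- Significance level: "A two-tailed significance level (α) of 0.05 was used".
- Power: "of 80% was targeted (β = 0.2").
- Effect: "The expected between-group difference (Δ) was three points, with a common standard deviation (σ) of five points".
- Size: "22 participants were required per group, yielding an initial total sample size of 44". A 10% allowance for dropout raises this to 50, that is, 25 per arm.

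The same section claims at least 80% power for both primary domains, gut microbiota and brain function. No rule in the article says how many of the five indicators must be significant for the trial to succeed.

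**The concern.** Single-step Bonferroni holds each of the five indicators to 0.01 whatever the other four show. Holm's procedure relaxes the threshold after each rejection, needs no additional assumption and protects the family-wise error equally well.

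The trial is small, and its hypothesis is that stimulation acts on gut and brain together. A conclusion about the gut-brain axis would be most convincing with a rejection in each domain. The second and later rejections are where a step-down test can gain. What is at stake is a few points of power for those rejections. The validity of the primary analysis is not in question.

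**Working it through.** **1. The plan's figure.** 0.05/5 = 0.01, as stated. If all five nulls are true and the tests are independent, the family-wise error is 1 − 0.99⁵ = 0.049. Under any dependence it is at most 5 × 0.01 = 0.05.

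**2. Holm's thresholds.** Order the five P values from smallest to largest and compare them with 0.05/5, 0.05/4, 0.05/3, 0.05/2 and 0.05/1, that is, 0.01, 0.0125, 0.0167, 0.025 and 0.05. Stop at the first failure.

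- *Never fewer rejections.* If an indicator has P ≤ 0.01, every smaller P value is also ≤ 0.01 and passes its own threshold, which is at least 0.01. Holm therefore reaches that indicator and rejects it.
- *Same error control.* With m₀ true nulls, at most 5 − m₀ hypotheses come before the first true null, so its threshold is at most 0.05/m₀. The chance of any false rejection is then at most m₀ × 0.05/m₀ = 0.05, with no assumption about dependence.
- *Same first step.* The smallest P value faces 0.01 under both methods, so the chance of at least one rejection is identical.

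**3. Inputs for the size of the gain.**

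- Standardised effect: 3/5 = 0.6 (section 3.3).
- Evaluable patients: 22 per arm, the plan's stated requirement. The expected dropout gives nearly the same number: 25 × 0.9 = 22.5.
- Correlation between indicators: not given, so assumed at 0 and 0.5.
- Number of indicators that truly respond: not given, so varied.

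**4. One test at 0.01.** The noncentrality is 0.6 × √(22/2) = 1.99, with 42 degrees of freedom and a critical t of 2.698. Power is 25%. (The normal approximation gives Φ(1.99 − 2.576) = 28%.)

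**5. Simulation.** Five normal indicators, two-sample t-tests, 60,000 trials per scenario, 22 per arm, 0.6 SD. Ranges cover correlation 0 to 0.5.

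| Indicators affected | Average power per affected indicator, Bonferroni | Same, Holm | At least one rejection, either method |
|---|---|---|---|
| 1 | 25–26% | 25–26% (gain about 0.1 point) | 28% |
| 2 | 25% | 26% | 40–46% |
| 3 | 25% | 27.0–27.6% | 48–59% |
| 5 | 25% | 29–31% | 58–77% |

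In every simulated trial Holm rejected all that Bonferroni rejected. With no indicator affected, family-wise error was 4.4–4.8%, identical for both methods. With three affected and two true nulls it was 1.8–2.0% for Bonferroni and 2.5–2.8% for Holm. Holm uses more of the 5% allowance but does not exceed it.

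**6. If nobody drops out.** At 25 per arm and 0.6 SD, average power goes from 30% to 35–37% with all five affected, from 30% to 32–33% with three, and stays at 30% with one.

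**The case against.** The strongest reply is that nothing here is wrong. Bonferroni is standard, prespecified, correctly computed and valid under any dependence, and the article does not contradict it. It also gives every indicator one fixed threshold and a matching 99% confidence interval. Preferring Holm is then a preference between two valid methods. This stands as to severity, and it rules out any claim that power is given up for nothing. It does not remove the fact that Holm rejects at least as much under the same error guarantee.

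A reader might infer a much larger benefit. With 25 per arm and all five indicators affected, average power would rise from 56% to 66–68% at 0.8 SD, and from 80% to 88–91% at 1.0 SD. The documents do not support using those figures: the only effect they assume is 0.6 SD, and they expect dropout. The chance of showing all five indicators also improves under Holm, but the article sets no such goal.

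A reader might also infer that Holm would bring the trial near its 80% target. It would not. Per-indicator power stays at about 31% or below with 22 per arm. Section 3.3 has its own problem. Its inputs give 2 × (2.80 × 5/3)² = 43.6, so 44 per group where the article has 22, and the sizing used 0.05 although primary tests are to run at 0.01. Changing the multiplicity procedure repairs neither.

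Finally, section 3.9.1 does not name the five indicators, and the gain depends on how many there are and how many respond. That limits the precision of the estimate. Holm's advantage itself holds for any final list.

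**Conclusion.** The point holds as an optional improvement to a valid plan. At the plan's 0.6 SD and 22 evaluable per arm, Holm adds about 4 to 6 percentage points of average power per affected indicator if all five respond, about 2 points if three respond, and practically nothing if one responds. It does not alter the chance of at least one significant primary indicator.

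That Holm never rejects less and keeps the 5% family-wise error is a mathematical result. It applies to any valid P values, including those from the mixed models in section 3.9.2. The size of the gain rests on assumptions: normal outcomes, two-sample t-tests, the same 0.6 SD on each affected indicator, and a correlation of 0 to 0.5, which the article does not give.

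**What to change.** In section 3.9.1 item ②, by a dated amendment before unblinding, replace the Bonferroni wording for the primary outcome with: *Holm step-down procedure at family-wise two-sided α = 0.05 over the primary indicators (ordered thresholds 0.01, 0.0125, 0.0167, 0.025 and 0.05 for five).* Report Holm-adjusted P values.

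The cost is one sentence, with no extra patients, data or modelling. The downside is that confidence intervals matching Holm's decisions are less simple. The 99% Bonferroni intervals can still be reported, labelled as conservative, with a note that an indicator rejected at a later Holm step may have a 99% interval that includes no difference. The sample-size calculation in section 3.3 needs its own correction.

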### Design

3.1

This is a single-center, randomized, investigator-blinded, sham-controlled trial. The protocol was registered with the Chinese Clinical Trial Registry (ChiCTR2500102345) on 13 May 2025 and approved by the Ethics Committee of Guangdong Provincial Hospital of Traditional Chinese Medicine (Approval No. ZF2025-162-01) on 18 April 2025. The study will be conducted in accordance with the Declaration of Helsinki. A total of 50 eligible postoperative AD patients will be recruited from the hospital and randomized to receive either active taVNS or sham stimulation. The study flow is outlined in Figure 1, and the schedule of events is presented in Table 1.

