#### Main statistical models

3.9.2

Mixed-effects models will serve as the core analytical framework to handle repeated measures collected at 1 day, 7 days, 4 weeks, and 24 weeks postoperatively. ① A linear mixed-effects model will be used for continuous outcomes, including gut microbiota indices (Shannon index, Bifidobacterium abundance), brain function parameters (fNIRS rCBF, EEG α-wave power), and biochemical markers (IL-6, TNF-α, 5-HT, and BDNF). ② A logistic mixed-effects model will be applied to binary outcomes, such as adverse events (SAE, skin allergy) and intestinal function recovery (first flatus within 48 h, first defecation within 72 h). ③ An ordinal logistic mixed-effects model will be used for ordinal outcomes, including scale scores (GIDS, HAMA, and HAMD).

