
The innovations of this study are reflected in three aspects: First, the combination of taVNS and the GBA theory is applied to the postoperative management of AD for the first time, overcoming the limitations of traditional single-system interventions by regulating complications through the synergistic actions of neural, immune, and endocrine pathways. Second, a multidimensional outcome indicator system is utilized, which includes not only core GBA biomarkers such as gut microbiota diversity and inflammatory factors but also, through collaboration with the rehabilitation department, real-time monitoring of brain function changes via BCI and fNIRS, enabling cross-system correlation analysis of intestinal function, inflammation, and brain function in postoperative patients. Third, a randomized controlled design is strictly followed: a sham stimulation control (with no current output, targeting non-vagus nerve innervated areas) is implemented, and stratified randomization based on the Stanford classification is employed to reduce bias and enhance the reliability of the results.

From a methodological perspective, the intervention protocol in this study is rigorously designed. For taVNS, the stimulation sites are selected as the cymba conchae or tragus (areas rich in the auricular branches of the vagus nerve), and the parameters are set to a frequency of 15 Hz and a pulse width of 200 μs—based on international standards and previous anti-inflammatory research evidence—to ensure the stimulation intensity is within patients' tolerance range while effectively activating the vagus nerve pathway. The sample size estimation is based on effect sizes of gut microbiota and inflammatory factor changes reported in similar studies; after accounting for a 10% dropout rate, 25 cases per group were determined, meeting statistical power requirements. The procedures for collecting and processing biological specimens (e.g., fecal samples stored at −80 °C, metagenomic sequencing for gut microbiota structure analysis) are standardized, and analyses are conducted by third-party laboratories to ensure data objectivity.

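### The gut–inflammation–brain association analysis names multiple linear regression for markers measured four times per patient, and the plan's mixed-model framework is not extended to it

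*Protocol article*

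**What the plan says.** Section 3.9.1, item ③ is one sentence: "Multiple linear regression will be used to explore associations between clinical outcomes, gut microbiota, inflammatory markers, and brain function". It names no visit, no choice between level and change, no covariates and no patient effect.

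Table 1 schedules IL-6, TNF-α, 5-HT, BDNF, gut microbiota, BCI and NIRS at Visits 2, 4, 5 and 6. Section 3.9.2 gives the matching time points and the model for them: "Mixed-effects models will serve as the core analytical framework to handle repeated measures collected at 1 day, 7 days, 4 weeks, and 24 weeks postoperatively". It then lists much the same variables, as outcomes: "A linear mixed-effects model will be used for continuous outcomes, including gut microbiota indices (Shannon index, Bifidobacterium abundance), brain function parameters". It does not mention the association analysis.

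Section 3.1 sets the number of patients: "A total of 50 eligible postoperative AD patients will be recruited". The Discussion presents the multidimensional outcome system as one of three innovations, "enabling cross-system correlation analysis of intestinal function, inflammation, and brain function in postoperative patients".

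**The concern.** The article deals with within-patient dependence where it compares outcomes over time. It then names a method without that provision where it relates the same repeated markers to each other. Item ③ is the only stated analysis linking gut, inflammation and brain, so any statement about a gut–brain mechanism would lean on it.

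Three things can go wrong, depending on how the sentence is carried out:

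- Pooled visits make the standard errors too small.
- Recovery after surgery that is common to all patients can look like a link between markers.
- With no arm term, two separate effects of stimulation can look like one pathway.

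Item ④ of the same section applies two-sided 0.05 to all tests unless a multiplicity adjustment says otherwise. Item ② assigns false-discovery-rate control to secondary outcomes, biomarkers and subgroups, and does not name the association analysis.

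**Working it through.** The plan states no figure for this analysis, so there is none to reproduce. The check asks how linear regression behaves under each way of carrying out item ③.

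**Inputs from the article:** 50 patients, 25 per arm, four time points (at most 50 × 4 = 200 patient-visits), two-sided 0.05. The sample size section gives a difference of 3 and an SD of 5, i.e. 3/5 = 0.6 SD.

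**Assumed, because the article gives none:** within-patient correlation ρ of 0.3, 0.5 or 0.7; shared recovery of 0 or 1 SD between first and last visit; a true slope of 0.25 between standardised markers where detection is examined.

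**1. Visits pooled, no shared recovery, markers unrelated.** If both markers have within-patient correlation ρ, the true variance of the slope exceeds the reported one by about 1 + (4 − 1)ρ². The actual error is then 2 × [1 − Φ(1.96/√(1 + 3ρ²))].

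| ρ | 1 + 3ρ² | 1.96/√ | Error by formula | Simulated |
|---|---|---|---|---|
| 0.3 | 1.27 | 1.74 | 8.2% | 8.2% |
| 0.5 | 1.75 | 1.48 | 13.8% | 13.0% |
| 0.7 | 2.47 | 1.25 | 21.2% | 21.6% |

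At ρ = 0.05 a separate simulation gives 5%, so the problem depends on appreciable within-patient correlation.

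**2. Visits pooled, 1 SD shared recovery, no visit term.** For a linear course (0, 1/3, 2/3, 1) the visit means have variance (0.250 + 0.028 + 0.028 + 0.250)/4 = 0.139. This induces a correlation of 0.139/1.139 = 0.122. With 200 rows, atanh(0.122) × √197 = 1.72, and Φ(1.72 − 1.96) = 0.41 before any allowance for within-patient correlation. Simulation with that correlation gives 43.2%, 43.6% and 45.3% at ρ = 0.3, 0.5 and 0.7. A second simulation, with most of the recovery early, gives 42–47%. Adding visit terms removes this part but leaves 8.6%, 14.0% and 21.2%.

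**3. One row per patient, arm included.** Using a single visit, a change score or a patient mean, simulated error is 4.1–5.8% in every scenario, including 1 SD of shared recovery, because the common recovery goes into the intercept.

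The cost is information. With slope 0.25 and unit residual SD, the correlation is 0.25/√(1 + 0.25²) = 0.243. With 50 rows, atanh(0.243) × √47 = 1.70, and Φ(1.70 − 1.96) = 0.40. Simulation gives 36–42%. A random-intercept model with visit and arm on all four visits gives about 92% detection with 4–6% error. That comparison assumes the same slope within and between patients.

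Four separate visit-wise regressions would give up to 1 − 0.95⁴ = 19% chance of at least one false positive per marker pair if the visits were independent, and less if they are correlated.

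**4. One row per patient, no arm term.** Suppose stimulation shifts both markers by d SD and they are otherwise unlinked. With equal arms the induced correlation is (d²/4)/(1 + d²/4).

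| d | Correlation | atanh × √47 | Rejection by formula | Simulated |
|---|---|---|---|---|
| 0.6 | 0.083 | 0.57 | 8.8% | 8.8% |
| 0.8 | 0.138 | 0.95 | 15.8% | 15.8% |
| 1.0 | 0.200 | 1.39 | 28.5% | 29.4% |

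With an arm term the rate returns to 4.9–5.2%.

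**The case against.** The strongest reply is that item ③ does not say what it could be faulted for. A reader might infer that the plan counts repeated values as independent patients. The article never says that visits are stacked, and never says that arm or visit terms are left out. Multiple regression admits covariates, and one row per patient is an equally natural reading that keeps the nominal error. Authors who write "Mixed-effects models will serve as the core analytical framework" for repeated data are not obviously planning to ignore repetition elsewhere. The visit and the covariates are details that an article may leave to the full plan. All of this stands, so the pooled-visit figures can only be stated conditionally.

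Two further replies also stand. The analysis is described as exploratory and carries no primary conclusion. A model aimed only at the within-patient coefficient would also be too narrow: between-patient association is a legitimate question, and time to first flatus or defecation has one value per patient.

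These replies do not rescue the choice of method. The article does name a method, and on each reading it does worse than the framework that section 3.9.2 already adopts. Pooling inflates error, while one row per patient gives up most of the chance of detecting a real association. Leaving out the arm term, which the text permits, confuses parallel effects with a link.

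**Conclusion.** The point holds in a limited form: for the repeated markers, the method named in item ③ is weaker than the one the plan already uses for the same variables.

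- **If visits are pooled:** false associations about 8–22% of the time for ρ of 0.3–0.7, and about 42–47% with 1 SD of shared recovery and no visit term.
- **If one row per patient is used with an arm term:** error near 5%, but about 40% rather than 92% detection of a slope of 0.25.
- **If one row per patient is used without an arm term:** about 9–29% false links when stimulation shifts both markers by 0.6–1.0 SD.

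The correlations, recovery size and slope are assumptions. The 0.6 SD comes from the article's sample size section. The article does not support saying that inflation will occur, because it does not fix the data level. It also does not support saying that the trial's main conclusions are at risk: the randomised comparisons of microbiota and brain function do not use this regression. What is affected is the weight that the cross-system findings can bear. The change is worth making before analysis.

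**What to change.** Replace item ③ with wording to this effect:

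- For markers measured at several visits, associations will be estimated with linear mixed-effects models with a patient random intercept and fixed effects for visit, arm and Stanford type. Within-patient and between-patient coefficients may be reported separately.
- For outcomes with one value per patient, such as time to first flatus or defecation, multiple linear regression with arm and Stanford type will be used.
- These associations are exploratory and do not by themselves establish mediation through the gut–brain axis.

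The cost is a few sentences and slightly more programming, with no new data or patients. Compared with pooled regression, there will be fewer nominally significant associations.
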